## Abstract

**Introduction::**

Retinal vein occlusion refers to diseases with decreased vision, dilated tortuous retinal veins visible on the fundus, and retinal hemorrhage, edema, and osmosis distributed along the vein. There is still no ideal intervention to treat central retinal vein occlusion. This study plan to observe the efficacy of Dan-Hong Hua-Yu oral solution in treating non-ischemic retinal vein occlusion, in order to provide new treatment ideas.

**Methods/Design::**

We plan to use random number table method, 64 cases of non-ischemic central retinal vein occlusion that meet the inclusion criteria will be randomly divided into a treatment group and a control group. The intervention group will be treated with Dan-Hong Hua-Yu oral solution according to the syndrome differentiation of Traditional Chinese medicine and the patient's fundus condition. Each group will take 4 weeks as a course of treatment and three consecutive courses of treatment without any interval during the course of treatment. Changes of visual acuity, fundus performance, and total clinical symptoms of patients before and after treatment will be observed.

**Discussion::**

This study will observe the efficacy of Dan-Hong Hua-Yu oral solution in the treatment of non-ischemic central retinal vein occlusion, with a view to providing new treatment ideas.

**Trial registration::**

ClinicalTrials.gov, ChiCTR2000030625, Registered on March 08, 2020.

## Introduction

1

Retinal vein occlusion (RVO) refers to diseases with decreased vision, dilated tortuous retinal veins visible on the fundus, and retinal hemorrhage, edema, and osmosis distributed along the vein.^[1]^ According to the site of occlusion, it can be divided into central branch retinal vein occlusion (CRVO) and branch retinal vein occlusion (BRVO). CRVO can be divided into ischemic and non-ischemic.^[2,3]^ RVO is a common retinal vascular disease in ophthalmology, and it is one of the major blinding fundus diseases. Due to the slow speed of venous blood flow, its severity is not as severe as that of arterial occlusion, but the venous occlusion has a longer incubation period, slow onset, and long course of disease, and its condition is very stubborn.^[4,5]^ Macular edema is the main complication of this disease, and vision often fails to recover. And, if the non-ischemic CRVO is not treated properly or timely, it can easily be converted into ischemic RVO, causing severe visual impairment.

The pathogenic factors of CRVO are relatively complex, and the etiology and pathogenesis are still unclear. According to previous surveys and studies, gender, age, hypertension, diabetes, atherosclerosis, cholesterol, high homocysteine, abnormal blood coagulation, glaucoma, refractive error, and intraocular pressure are all caused by retinal vein occlusion.^[6]^Among them, RVO is closely related to systemic diseases such as hypertension, diabetes, atherosclerosis, and high cholesterol. The CRVO is mostly related to hypertension, arteriosclerosis, high blood viscosity, and high intraocular pressure.^[7]^ The incidence of RVO is closely related to age, and its incidence increases with age. The recent studies have shown that the average age of onset of retinal vein occlusion is 64.8 years, while the average age of cases observed in China is 57.08 years.^[8,9]^ According to statistics, the incidence of RVO in China is as high as 1.9%, and an estimated 160 million people worldwide suffer from RVO.^[10,11]^ In recent years, with the improvement of people's living standards, changes in dietary structure, increased work and stress, and the acceleration of the pace of modern life, the incidence of this disease has increased, and its age of onset is getting lower and lower.^[12]^

The pathogenesis of CRVO is not very clear. The current treatment of CRVO is not ideal. Modern medicine now recognizes the treatment methods mainly to remove the cause, local and systemic treatment. Current treatment methods include laser therapy, vitreous cavity drug injection, combined therapy, hyperbaric oxygen therapy, surgical therapy, and drug therapy. Most modern medical treatments are aimed at preventing and treating complications, but the role of vision preservation and improvement is still controversial.^[13]^ At present, the surgical treatment of modern medicine, such as optic disc radial incision, its therapeutic effect and safety need to be further determined.^[14,15]^ The Traditional Chinese medicine (TCM) combined with the local ophthalmology syndrome at the same time as the whole body syndrome differentiation makes its treatment more complete. Because TCM has certain advantages in the treatment of CRVO, this study observed statistical changes in visual acuity, bleeding absorption range, and improvement of TCM symptoms of Dan-Hong Hua-Yu oral solution in the treatment of non-ischemic CRVO patients. We aim to provide new therapeutic ideas for the treatment of non-ischemic CRVO.

## Methods/Design

2

### Study design and settings

2.1

This study will be a single-blinded, randomized controlled trial with two parallel groups. It will be conducted at the Beijing Hospital of Traditional Chinese Medicine, Capital Medical University. This protocol was written and based on Standard Protocol Items: Recommendations for Interventional Trials guidelines. If they agree, they will sign an informed consent form. Only those participants who read and agree to the protocol and who sign the informed consent form will take part in the study, following the schedule described in Figure 1.

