### Interventions

2.4

The statistically significant minimum sample size for clinical trials requires no less than 30 patients in each group. For the selected cases that met the inclusion criteria and were screened out by the exclusion criteria, the subjects were randomly divided into the intervention group (32 cases) and the control group (32 cases) by random number method.

Control group: Patients in the control group will be treated with Fufang Xueshuantong Capsule (Manufacturer: Guangdong Zhongsheng Pharmaceutical Co., Ltd.; Specification: 0.5 g). Usage: oral, 1.5 g once, three times a day.

Intervention group: This group will be given the TCM prescription-Dan-Hong Hua-Yu oral solution (Guangzhou Baiyunshan Hutchison Huangpu Traditional Chinese Medicine Co., Ltd.) 20 mL/time, oral, three times a day. The composition of Dan-Hong Hua-Yu oral solution is: *Dansheng*, *Honghua*, *Chuanxiong*, *Taoren*, *Danggui*, *Caihu*, *Zhiqiao*.

Each group will take 4 weeks as a course of treatment and three consecutive courses of treatment without any interval during the course of treatment. At the same time, closely monitor the change of the condition in order to control the deterioration of the condition in time.

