#### Efficacy evaluation

2.5.3

Refer to “Guidelines for Clinical Research of New Chinese Medicine”. Efficacy was evaluated by the ratio of the difference between the points before and after treatment compared to the points before treatment. Syndrome treatment efficiency (%) = (total points before treatment total points after treatment)/total points before treatment × 100.

(1)Clinical control: clinical symptoms and signs disappeared or basically disappeared, and syndrome scores were reduced by ≥95%;(2)Significant effect: clinical symptoms and signs were significantly improved, and syndrome scores were reduced by 70%;(3)The signs and symptoms have improved, and the syndrome scores have decreased by ≥30%;(4)Ineffective: the clinical symptoms and signs have not improved significantly, and the syndrome scores have decreased by <30%.

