### Randomization and blinding

2.7

The random method will use the closed envelope method for block randomization. Use the SAS software PROC PLAN procedure statement for random grouping. The subjects will be numbered 1 to 64 according to the order in which the patients were enrolled, and random numbers and assignments corresponding to the order of inclusion were obtained. The groups will be sealed in opaque envelopes, and the order of inclusion will be affixed to the surface of the envelopes. Randomization envelopes and distributions are performed by individuals who are not involved in treatment and evaluation.

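### The trial is labelled single-blinded, but its capsule-versus-liquid regimens cannot blind patients and the protocol names no one else as blinded

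*Protocol article*

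**What the plan says.** Section 2.1 (Study design and settings) gives the blinding level without qualification: "This study will be a single-blinded, randomized controlled trial with two parallel groups". No blinded party is named there.

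Section 2.4 (Interventions) describes the two regimens. For the control arm: "Patients in the control group will be treated with Fufang Xueshuantong Capsule", supplied in 0.5 g units, with "Usage: oral, 1.5 g once, three times a day". For the intervention arm: "This group will be given the TCM prescription-Dan-Hong Hua-Yu oral solution", given as "20 mL/time, oral, three times a day". Neither description mentions a placebo capsule, a placebo liquid or any disguise of form.

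Section 2.7 (Randomization and blinding) covers block randomization, a SAS-generated sequence and envelopes: "The groups will be sealed in opaque envelopes, and the order of inclusion will be affixed to the surface of the envelopes". The sentence closest to blinding is "Randomization envelopes and distributions are performed by individuals who are not involved in treatment and evaluation". The section does not say that patients, image readers, examiners or analysts are unaware of the group.

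On outcomes, section 2.5.1 makes fundus fluorescein angiography (FFA) primary. Section 2.5.2 lists best corrected acuity on an eye chart and fundus photography as secondary. Section 2.5.3 (Efficacy evaluation) grades response by the percentage fall in a syndrome score. Its top category requires "clinical symptoms and signs disappeared or basically disappeared, and syndrome scores were reduced by ≥95" per cent.

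**The concern.** Blinding is a stated property of this design, and readers of the results will rely on it. If the protocol is carried out as written, it is not clear that anyone is blinded. Patients can see what they are taking. Nothing shown keeps the people who read the angiograms, test acuity or score symptoms from learning the group.

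Two things are at stake. The trial could be reported as single-blind on a basis that the protocol does not provide. Several outcomes also leave room for judgement or expectation: symptom points depend on what patients say, chart acuity depends on the patient's effort and the examiner's encouragement, and image reading involves judgement. The two-group comparison in section 2.8 cannot separate a difference produced that way from a treatment effect.

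**Working it through.** The plan states no figure to reproduce. The check is whether the label in 2.1 is supported by the rest of the text for each party it could refer to.

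**Step 1: can patients be blinded?** Inputs are from 2.4. The control arm takes 1.5 g per intake from 0.5 g units, so 1.5 / 0.5 = 3 capsules. The intervention arm takes 20 mL of liquid. Both are taken three times a day. The frequency is the same, but three capsules and a 20 mL drink are plainly distinguishable. Without dummies, each patient knows which of the two forms they take. The same holds for anyone who hands out the product or sees it.

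**Step 2: are assessors blinded?** Section 2.7 contains two protections.

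- Opaque, numbered envelopes hide the next assignment until it is made. That is allocation concealment, and it ends once the envelope is opened.
- Envelope staff take no part in treatment or evaluation. This keeps the people who know the sequence away from assessment. It does not keep the assessors from learning the group afterwards, from the patient, the treating clinician or the record. Nor does it separate treating staff from evaluators, who could be the same people.

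**Step 3: put the readings side by side.**

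| Meaning of the label | Relevant text | Result |
|---|---|---|
| Patients blinded | 2.4: capsule versus liquid, no dummy | Contradicted |
| Outcome assessors blinded | 2.7: concealment and separate envelope staff only | Possible, but not stated |

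**Step 4: which outcomes are exposed?**

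- The symptom part of the syndrome score (2.5.3) is most exposed. It rests on reports from unblinded patients, so masking the assessor would not fully protect it.
- Chart acuity (2.5.2) depends on effort and on the examiner.
- FFA (2.5.1) and fundus photographs (2.5.2) are recorded images. They are the least exposed and the easiest to mask, but masked reading is not stated.

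**Step 5: illustration only.** The documents give no size for such a bias. Suppose knowledge of treatment shifts the mean difference by d standard deviations when there is no true effect, with n = 32 per arm (2.4, 2.6) and the two-sided 5% independent-samples t test of 2.8. The non-centrality parameter is d × √(n/2) = d × 4, with 62 degrees of freedom and critical value 1.999.

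| Assumed d | Non-centrality | Rejection probability |
|---|---|---|
| 0.20 | 0.8 | 12.4% |
| 0.25 | 1.0 | 16.6% |
| 0.30 | 1.2 | 21.9% |

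With the 20% drop-out that 2.6 allows (32 × 0.8 = 25.6, taken as 26 per arm), the same shifts give 10.9%, 14.3% and 18.6%. Both the size and the existence of the shift are assumed.

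**The case against.** The strongest reply is that no sentence says patients are blinded. Single-blinded is also used for assessor-blinded trials, and with a capsule against a liquid that is the natural reading. Keeping envelope staff out of evaluation is compatible with it. The article condenses a fuller protocol, and both figures are missing from the text shown, so the masking arrangements may be set out elsewhere. Moreover, the primary outcome is a recorded angiogram, which is less open to expectation than a symptom score. The comparator is itself an active manufactured product, so it is not obvious that expectation would favour the new one.

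Much of this stands. A reader might infer that assessors are unmasked, or that the label is simply untrue. The documents do not support either inference: 2.7 is silent on assessors, and silence is not evidence that they know the group. A reader might also infer that the false-positive rate is inflated to some definite level. The documents give neither a size nor a direction for any bias, so that does not follow either.

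The reply does not remove the point. The article has a section headed with the word blinding and describes both regimens, so this is more than a detail lost in condensation. A stated property lacks support in the very section meant to support it, and one ordinary reading of it conflicts with 2.4.

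**Conclusion.** The point holds in a limited form. As described, patients cannot be blinded, and the text names no other blinded party. The label in 2.1 is false if it means patients and unsupported if it means assessors.

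The conclusion about patients rests on one assumption: that 2.4 describes the regimens completely, with no dummies. The conclusion about assessors is only that their blinding is not stated.

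No numerical size can be attached from the documents. The rejection rates above show what an assumed bias would do and carry no weight in the conclusion. The practical weight falls on the symptom part of the syndrome score and on acuity, with a smaller but easily removed exposure for FFA. Where the syndrome score ranks among the endpoints is a separate question and is not decided here. This should be corrected before results are reported as single-blind.

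**What to change.** - **Sections 2.1 and 2.7:** state that patients and treating clinicians are not blinded and that blinding applies to outcome assessment. Name the assessors concerned.
- **Images:** code the angiograms and fundus photographs, which are taken anyway, and have them read without group label. This protects the primary outcome.
- **Acuity and syndrome points:** where existing staff allow, have them recorded by evaluators without access to the allocation.
- **Limitation:** acknowledge that the symptom part of the syndrome score is reported by unblinded patients, so masking the assessor does not fully protect it.

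The cost is a small amount of image coding and a blinding label that looks less favourable. Masked recording of acuity and symptoms may need staffing that the site does not have. Section 2.7 does not separate treating staff from evaluators, so it cannot be assumed that no extra person is needed. If masked recording is not feasible, the protocol should say that these two measures are not masked. No treatment, dose or visit changes.

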**Figure 1 F1:**
[figure not shown]
SPIRIT figure for the schedule of enrollment, interventions, and assessments.

### Ethical aspects

2.2

This study will be approved by Beijing Hospital of Traditional Chinese Medicine Ethics Committee. It will be conducted in accordance with the protocol. The rules of confidentiality will be respected. The study protocol is funded through a protocol registry. The study is supported by the TCM evidence-based capacity building project.

### Participants

2.3

All the cases in this study originated from the ophthalmology clinic and ward of Beijing Hospital of Traditional Chinese Medicine. Patients diagnosed with non-ischemic CRVO by clinical manifestations combined with fundus fluorescence angiography.

#### Diagnostic criteria

2.3.1

The diagnostic criteria for western medicine will be formulated with reference to the “*Chinese Ophthalmology*” published by the People's Medical Publishing House in 2014 and the “*Traditional Chinese Medicine Disease Diagnostic Effectiveness Criteria*” issued by the State Administration of TCM in 2017. The details are as follows:

(1)Vision loss to varying degrees;(2)(2) Fundus examination: normal or slightly blurred nipples, edema, dilated or tortuous veins, small or medium flaming retinas, and spot or sheet bleeding along the veins;(3)Macular normal or mild edema;(4)Fundus fluorescein angiography (FFA) shows prolonged retinal vein filling time, light capillary leakage, venous wall staining, no non-perfusion area, or neonatal blood vessels.

Non-ischemic CRVO is equivalent to the category of “blindness” in TCM. Therefore, the diagnostic criteria for TCM will refer to the standards of the Chinese medicine industry of the People's Republic of China for the “*Traditional Chinese Medicine Diagnosis and Efficacy Standards*”, the “Twelfth Five-Year Plan” Key Specialist Collaboration Group of the State Administration of TCM “*Diagnosis and Treatment of Blindness* (*Retinal Vein Occlusion*)” and “*Chinese Medicine Ophthalmology*” will be formulated.

#### Inclusion criteria

2.3.2

This study will be conducted in China. We will enroll participants based on the following inclusion criteria:

(1)Those who meet the diagnosis of traditional Chinese and western medicine CRVO and have no other fundus lesions;(2)Aged between 30 and 65 years;(3)The onset of disease is within 1 month, and can be treated for 3 months;(4)In the sign, after obtaining the consent of the patients and their families, they volunteered to participate in the research of this topic.

#### Exclusion criteria

2.3.3

Patients will be excluded, if they meet the following criteria:

(1)Combined with other eye diseases that affect the determination of efficacy;(2)Women during pregnancy or lactation;(3)Patients who have taken hormonal drugs in the past 3 months or have been treated with this research protocol;(4)People with severe heart, liver, and kidney dysfunction and mental disorders;(5)Subjects participating in other clinical studies.

#### Criteria for termination of trials

2.3.4

If the following happens, we will terminate the test: severe acute disease response, severe allergic reactions, and other adverse reactions; those who withdraw due to worsening or ineffective eye disease during treatment.

### Interventions

2.4

The statistically significant minimum sample size for clinical trials requires no less than 30 patients in each group. For the selected cases that met the inclusion criteria and were screened out by the exclusion criteria, the subjects were randomly divided into the intervention group (32 cases) and the control group (32 cases) by random number method.

Control group: Patients in the control group will be treated with Fufang Xueshuantong Capsule (Manufacturer: Guangdong Zhongsheng Pharmaceutical Co., Ltd.; Specification: 0.5 g). Usage: oral, 1.5 g once, three times a day.

Intervention group: This group will be given the TCM prescription-Dan-Hong Hua-Yu oral solution (Guangzhou Baiyunshan Hutchison Huangpu Traditional Chinese Medicine Co., Ltd.) 20 mL/time, oral, three times a day. The composition of Dan-Hong Hua-Yu oral solution is: *Dansheng*, *Honghua*, *Chuanxiong*, *Taoren*, *Danggui*, *Caihu*, *Zhiqiao*.

Each group will take 4 weeks as a course of treatment and three consecutive courses of treatment without any interval during the course of treatment. At the same time, closely monitor the change of the condition in order to control the deterioration of the condition in time.

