#### Primary outcome measures

2.5.1

*Fundus fluorescein angiography*. Inspection method: Tobiconamide eye drops in the conjunctival sac are fully dilated. Perform allergy tests on patients according to reagent requirements. If you are not allergic, push the sodium fluorescein stock solution into the vein and observe the patient's retinal vein filling with the fundus camera. Check before and after treatment.

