### Sample size calculation

2.6

This study is a small sample clinical trial. According to statistical requirements, there are at least 30 cases in each group. Considering that the drop-out rate does not exceed 20%, a total of 64 cases will be collected, of which 32 will be in the intervention group and the other in the control group.

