### Statistical analysis

2.8

According to the m-ITT principle, all randomized cases will be included. And there is at least one treatment and one post-baseline data. The missing data are not filled, and the actual observation values are used for statistical analysis. The measurement data are described by mean, standard deviation, median, and quartile. If the data meets the normal distribution, it is compared with the baseline value at the time of enrollment, and a paired *t* test is used. Differences in efficacy between the two groups will be compared using independent sample *t* tests. If the normal distribution is not satisfied, a non-parametric test is used. The count data is described using a composition ratio. If the normal distribution is satisfied, the changes before and after treatment in the two groups are tested by *X*^2^. If the normal distribution is not satisfied, a non-parametric test is used. The statistical software is SPSS 24.0, when *P* < .05, it showed that the difference is statistically significant.

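### The sample size of 64 rests on a claimed statistical minimum of 30 patients per group; no such requirement exists, so the stated basis is invalid and the adequacy of the size is unsupported

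*Protocol article*

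**What the plan says.** Section 2.4 gives the rule as a general fact about trials: "The statistically significant minimum sample size for clinical trials requires no less than 30 patients in each group". It then allocates 32 patients to each arm.

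Section 2.6 opens with "This study is a small sample clinical trial" and continues: "According to statistical requirements, there are at least 30 cases in each group". The total follows: "Considering that the drop-out rate does not exceed 20%, a total of 64 cases will be collected".

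Section 2.8 (Statistical analysis) names the between-arm test, "Differences in efficacy between the two groups will be compared using independent sample *t* tests", with non-parametric and chi-square alternatives, and sets significance at P below .05. The primary outcome in section 2.5.1 is fluorescein angiography before and after treatment, described as an instruction to "observe the patient's retinal vein filling with the fundus camera". It is given no measurement scale. The article states no target difference, standard deviation, event rate or power.

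**The concern.** Apart from the drop-out remark, the rule of 30 is the only reason given for the size, and it is stated twice as fact. It is not a fact. Statistical significance is a property of a test result, not of a sample size, and no count of patients per group meets a general statistical requirement.

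This is a wrong statement, not a detail left to a fuller document. A separate analysis plan could add a power calculation, but it could not make the rule true.

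What is at stake is how the result is read. Both arms receive an active oral medicine. A reader told that the size meets statistical requirements could take a non-significant between-arm comparison as evidence that the two medicines do equally well. The article gives no ground for that reading.

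**Working it through.** **Step 1: inputs.** From the article: 30 per arm as the claimed minimum (2.4, 2.6); 32 per arm and 64 in total (2.4, 2.6); drop-out up to 20% (2.6); P below .05 and an independent-samples t test (2.8). Assumed here, because the article does not give them: two-sided testing, 80% power, and every effect size.

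**Step 2: the plan's own figure.** No power formula can reproduce 64, because the inputs are not stated. The only derivation available is 30 per arm plus drop-out:
- dividing by (1 − 0.20): 30 / 0.80 = 37.5, so 38 per arm and 76 in total;
- multiplying by (1 + 0.20): 30 × 1.20 = 36 per arm and 72 in total;
- 32 per arm keeps 30 only if drop-out is at most 2 / 32 = 6.25%.

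So 64 does not follow from 30 and 20%. That is a separate arithmetic point, and correcting it would leave the rule of 30 in place. It matters here because it fixes how many patients may be analysed: 32 × 0.80 = 25.6, that is 25 to 26 per arm. Section 2.8 requires a post-baseline value and does not fill in missing data.

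**Step 3: can 30 be a general minimum?** Patients per arm for 80% power, two-sided 5% t test:

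| Assumed true difference | Needed per arm |
|---|---|
| 0.8 SD | 26 |
| 0.5 SD | 64 |
| 0.3 SD | 176 |
| 0.2 SD | 394 |

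The requirement varies about fifteen-fold (394 / 26 ≈ 15). Thirty is more than enough for the first row and far too few for the last.

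**Step 4: what the chosen size delivers.** By normal approximation the detectable difference in SD units is (1.960 + 0.842) × √(2/n). With n = 30 this is 2.802 × 0.2582 = 0.723; with n = 32 it is 2.802 × 0.2500 = 0.700. The noncentral t calculation, which matches the named test, gives slightly larger values:

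| Analysed per arm | Detectable at 80% power | Power for 0.5 SD | Power for 0.3 SD |
|---|---|---|---|
| 32 | 0.71 SD | 50% | 22% |
| 30 | 0.74 SD | 48% | 21% |
| 26 | 0.79 SD | 42% | 19% |
| 25 | 0.81 SD | 41% | 18% |

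**Step 5: sensitivity to the assumptions.** At 90% power the detectable difference is 0.82 SD with 32 per arm and 0.85 SD with 30. With a one-sided 5% test and 80% power (normal approximation) it is 0.62 and 0.64 SD. For a binary outcome with assumed rates of 60% and 80%, power with 30 per arm is about 39 to 40%.

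**The case against.** The strongest reply is that the article never claims adequacy. Section 2.4 gives a floor, which is a necessary condition, and section 2.6 openly calls the trial a small one. No power or detectable difference is stated that could be false. This stands. A reader might infer from the figures above that the trial is too small, or that the article asserts an adequacy which is untrue; the documents support neither. With a true difference of 0.8 SD, 26 per arm would suffice, and no target is named against which to judge 64.

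It is also fair that the figures rest on assumptions. The primary outcome has no stated scale, so an SD-based t-test calculation may not apply to it, and section 2.8 allows other tests. The figures are therefore illustrative only. A condensed article may also leave power inputs to the full protocol, so their absence carries no weight here.

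Finally, the misreading of a null result is a risk, not something the article commits to: it makes no equivalence or non-inferiority claim. That limits the harm but does not rescue the rule. Calling the trial small does not cure it either, because the next sentence says that statistical requirements set the number.

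**Conclusion.** The point holds as a finding about the justification. That 30 per group is not a statistical minimum or requirement needs no assumption. The basis given for 64 patients is therefore invalid, and the statistical adequacy of that number is unsupported, which is not the same as shown to be inadequate.

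The illustrative size of the problem is a detectable difference between about 0.71 SD (no loss) and 0.81 SD (loss at the protocol's own ceiling), with power for 0.5 SD between about 50% and 41%. This is conditional on a two-sided 5% t test, 80% power for the detectable difference, and a continuous outcome. The error affects what can be concluded from a null result. It does not affect the allocation or the analysis, and it should be corrected.

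**What to change.** Delete the statements in sections 2.4 and 2.6 that present 30 per group as a minimum or a statistical requirement. In section 2.6, give the sponsor's actual basis for 64. Feasibility is one possibility, but only the sponsor can say so. Then state what the size delivers, with the assumptions labelled, for example:

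*The sample size of 64 was chosen because [sponsor's reason]. Assuming a two-sided 5% t test and 80% power, the detectable between-arm difference is about 0.71 SD with 32 analysed per arm, 0.74 SD with 30, and 0.79 to 0.81 SD with the 25 to 26 per arm that remain at 20% drop-out. Power for an illustrative difference of 0.5 SD is about 50%, 48% and 41 to 42% respectively. A non-significant between-arm result will be reported as inconclusive and not as evidence of no difference.*

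The drop-out line is needed, because quoting only 32 per arm would overstate what the trial delivers under its own allowance. The cost is a short edit to two sections. No patients are added, and the design and analysis do not change. The downside is a less favourable statement of what the trial can show.
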